## STUDY RATIONALE

Previous in vitro and pre-clinical studies have provided the scientific rationale for the use of RELiZORB for the treatment of SBS. RELiZORB was approved by the FDA for use in children older than age 5 and adults to hydrolyze fats in enteral formula. Furthermore, the FDA has reviewed this study and determined it to be nonsignificant risk.

***Representative Fat Hydrolysis Data Using RELiZORB***

RELiZORB has been shown to hydrolyze >90% of fat in most enteral formulas when tested with 500 mL of enteral formula at a flow rate of 120 mL/hour (Table 1). Comparable or improved fat hydrolysis has also been shown when RELiZORB was used with enteral feeding pump flow rates between 10-120 mL/hour.

Table 1. **Fat hydrolysis for representative enteral formulas (500 mL) using RELiZORB at a flow rate of 120 mL/hour**

| **PRODUCT** | **FAT (g)** | **MCT / LCT RATIO (%)** | **CALORIES (kcal)** | **OMEGA-3 DHA & EPA (g)** | **% FAT HYDROLYSIS WITH RELiZORB** |
| --- | --- | --- | --- | --- | --- |
| **NUTREN** **2.0** | 52 | 74:25 | 1,000 | - | >90% |
| **TWOCAL** **HN** | 43 | 19:81 | 950 | - | 60% |
| **IMPACT** **PEPTIDE 1.5** | 32 | 50:50 | 750 | 2.45 | >90% |
| **PEPTAMEN** **1.5** | 28 | 70:30 | 750 | - | >90% |
| **PEPTAMEN AF** | 27 | 50:50 | 600 | 1.2 | >90% |
| **VITAL AF 1.2 CAL** | 26 | 45:55 | 570 | 1.9 | >90% |
| **PEPTAMEN** | 20 | 70:30 | 500 | - | 90% |
| **NUTREN**® **1.0** | 19 | 25:75 | 500 | - | >90% |

(For a detailed list of compatible formulas refer to <https://www.relizorb.com/docs/pdfs/Compatible-Formulas-and-Pumps.pdf>, accessed September 29, 2020)

The efficacy, safety and intended use of RELiZORB was tested in a well-established pre-clinical porcine model of exocrine pancreatic insufficiency (EPI) that mimics the inability to digest and absorb fats.^18^ Ligation of the pancreatic ducts in the EPI porcine model causes a total lack of pancreatic enzymes, leading to arrested growth, fatty acid deficiencies, and GI symptoms including steatorrhea.

In a study conducted in the EPI porcine model, a single feeding (500 mL; 4 hours, 120 mL/hr) of enteral formula administered through RELiZORB resulted in an increase in fat absorption, caloric intake and improvement in uptake of omega-3 fatty acids docosahexaenoic acid (DHA) and eicosapentaenoic acid (EPA) in plasma levels over 24 hours compared with enteral formula that was not administered through RELiZORB. Enteral formula passed through RELiZORB normalized plasma levels of DHA and EPA compared to the healthy control group. RELiZORB was shown to hydrolyze >90% of fats from 500 mL of Peptamen AF® (750 kcal, 32 g fat, 1.8 g DHA and EPA; Nestlé Health Science Europe). The clinical significance of these findings has not been determined.

The objective of this study (i.e., *24 Hour Pharmacokinetic Plasma Fatty Acid Uptake: Safety, tolerability and fat absorption with use of RELiZORB in enteral (tube) feeding*) was to measure fat absorption by assessing plasma 24-hour pharmacokinetic changes evaluated by measuring important plasma long-chain polyunsaturated fatty acids (LCPUFA), specifically omega-3 fatty acids DHA and EPA. This was a parallel study consisting of three groups: an EPI group (n=6) receiving formula hydrolyzed with RELiZORB, a second EPI group (n=5) receiving non-hydrolyzed formula without RELiZORB and a third healthy control group (n=3) with normal digestive function receiving non-hydrolyzed formula without RELiZORB. Peptamen® AF, a semi-elemental enteral formula containing hydrolyzed protein was provided over 4 hours (500 mL; pump rate 120 mL/hour). Fat absorption was evaluated by measuring plasma long-chain polyunsaturated fatty acids (LCPUFA), specifically plasma DHA and EPA levels. RELiZORB use was well tolerated in the porcine model with normal food intake and no serious adverse reactions. No vomiting or diarrhea was recorded during the 24-hour period. RELiZORB normalized plasma levels of DHA and EPA compared to the healthy control group. Formula hydrolyzed with RELiZORB was associated with a statistically significant increase in total fat absorption and improvement in uptake of omega-3 fatty acids (DHA and EPA) in plasma levels over 24-hours compared with non-hydrolyzed formula without RELiZORB (*P* < 0.05). The clinical significance of this observation has not been determined. Increased uptake of specific long-chain polyunsaturated fatty acids with use of RELiZORB resulted in a statistically significant reduction in the omega-6 to omega-3 ratio. The clinical significance of this observation has not been determined.

Based on the EPI porcine model data, the FDA approved RELiZORB in November 2015 for use in adults to hydrolyze fats in enteral nutrition. The first clinical study (*Increased Fat Absorption from Enteral Formula through an In-line Digestive Cartridge in Patients with Cystic Fibrosis*) assessed the safety, tolerability and fat absorption of RELiZORB in patients with cystic fibrosis (CF). This was a multicenter, randomized, double-blind, crossover trial with an open-label safety evaluation period. The study was comprised of a 7-day run-in period, a cross-over period, and a 7-day open-label safety period. Patients were randomized to receive RELiZORB or a placebo cartridge. The primary efficacy endpoint was the change in plasma fatty acid concentrations of DHA and EPA, markers of fat absorption, for 24 hours after a single enteral nutrition feeding administered through the in-line device. Safety and tolerability endpoints included gastrointestinal (GI) events associated with fat malabsorption, as well as non-GI events.

Thirty-three patients were enrolled from 11 CF centers across the United States; 82% of enrolled patients were ≤18 years of age. The mean area under the curve for total DHA + EPA was 2.8 times higher for RELiZORB compared to placebo (537.0±400.5 vs 192.2±198.7 µg/mL, respectively; *P*<0.001). RELiZORB was generally safe and well tolerated, with no unanticipated adverse effects.

Freedman et al evaluated safety, tolerability, and fat absorption of the RELiZORB enzyme cartridge in 33 patients aged 5 – 34 years with cystic fibrosis^20^. In this multicenter, randomized, double-blind, crossover trial, plasma omega-3 fatty acid concentrations were used to measure fat absorption. The RELiZORB enzyme cartridge was associated with a 2.8-fold increase in plasma omega-3 fatty acid concentration compared to placebo and was determined to be safe and well-tolerated.

In another study by Stevens et al, 36 cystic fibrosis patients aged 5 – 33 years were followed longitudinally for 90 days in a multicenter, open-label study of RELiZORB use with overnight enteral nutrition^21^. The RELiZORB enzyme cartridge was associated with a 2-fold increase in the omega-3 index, a long-term measure of fat absorption in patients with cystic fibrosis. No unexpected adverse events were associated with the use of the RELiZORB cartridge.

# OBJECTIVES

## PRIMARY OBJECTIVE

- To determine the effectiveness of the RELiZORB enzyme cartridge on the absorption of enteral nutrition when used daily for a total 90 days of treatment, in pediatric subjects with SBS who are PN dependent, aged 2 years – 18 years, by measuring the change in PN calories from baseline, assessed weekly throughout the study.

## SECONDARY OBJECTIVE

- To determine the effectiveness of the RELiZORB enzyme cartridge on the absorption of enteral nutrition when used daily for a total 90 days of treatment, in pediatric subjects with SBS who are PN dependent, aged 2 years – 18 years, by measuring the change in body weight (weight-for-age z-score) from baseline, assessed weekly throughout the study.

## SAFETY OBJECTIVES

- To determine the safety and tolerability of the RELiZORB enzyme cartridge on the absorption of enteral nutrition when used daily for a total 90 days of treatment, in pediatric subjects with SBS who are PN dependent, aged 2 years -18 years, by recording daily the incidence of adverse events, including changes in stool consistency (through Bristol scale), changes in stool amount/frequency (if applicable), increased ostomy output (if applicable, defined as >2.5 mL/kg/hour), the need to decrease enteral feeds, changes in urine color (through Dehydration Color scale), and discontinuation from study treatment.
- To determine the safety and tolerability of the RELiZORB enzyme cartridge on the absorption of enteral nutrition when used daily for a total 90 days of treatment, in pediatric subjects with SBS who are PN dependent, aged 2 years -18 years, by monitoring vital signs (blood pressure, pulse rate, respiratory rate, temperature).
- To determine the safety and tolerability of the RELiZORB enzyme cartridge on the absorption of enteral nutrition when used daily for a total of 90 days of treatment, in pediatric subjects with SBS who are PN dependent, aged 2 years – 18 years, by monitoring hematology and biochemistry parameters. Clinical lab evaluations will include sodium, potassium, chloride, CO2, glucose, blood urea nitrogen (BUN), creatinine, calcium, phosphorus, magnesium, alkaline phosphatase, albumin, pre-albumin, total protein, total and direct bilirubin, AST, ALT, GGT, triglycerides, cholesterol, high-density lipoprotein (HDL), very low-density lipoprotein (VLDL), low-density lipoprotein (LDL), C-reactive protein (CRP), and fatty acid profile.

## EXPLORATORY OBJECTIVES

- To evaluate the effect of using the RELiZORB enzyme cartridge with enteral nutrition when used daily for a total 90 days of treatment, on the change in fat absorption as measured by 72-hour total fecal fat and fatty acid composition in pediatric subjects with SBS who are PN dependent, aged 2 years – 18 years.
- To evaluate the effect of using the RELiZORB enzyme cartridge with enteral nutrition when used daily for a total 90 days of treatment, on the change in plasma fatty acid composition and fat-soluble vitamins (A, D, E, and K) in pediatric subjects with SBS who are PN dependent, aged 2 years – 18 years.
- To evaluate the effect of using the RELiZORB enzyme cartridge with enteral nutrition when used daily for a total 90 days of treatment on growth in pediatric subjects with SBS who are PN dependent, aged 2 years – 18 years, by measuring height (assessed with height-for-age z-score) and head circumference (assessed with head circumference-for-age z-score in children < 36 months of age).
- To evaluate the effect of using the RELiZORB enzyme cartridge with enteral nutrition when used daily for a total 90 days of treatment on BMI z-score in pediatric subjects with SBS who are PN dependent, aged 2 years – 18 years.
- To evaluate the effect of using the RELiZORB enzyme cartridge with enteral nutrition when used daily for a total 90 days of treatment on PN dependency in pediatric subjects with SBS who are PN dependent, aged 2 years – 18 years, by recording PN volume.
- To evaluate the effect of using the RELiZORB enzyme cartridge with enteral nutrition when used daily for a total of 90 days of treatment on enteral nutrition tolerance in pediatric subjects with SBS who are PN dependent, aged 2 years – 18 years, by recording total enteral calories and volume.
- To evaluate the effect of using the RELiZORB enzyme cartridge with enteral nutrition when used daily for a total of 90 days of treatment on oral nutrition tolerance in pediatric subjects with SBS who are PN dependent, aged 2 years – 18 years, by recording total oral calories and volume.
- To evaluate the effect of using the RELiZORB enzyme cartridge with enteral nutrition when used daily for a total of 90 days of treatment on the ability to wean from PN at any time during the course of the study.

# STUDY DESIGN

## BASIC DESIGN CHARACTERISTICS

This study is a phase 3, open labeled uncontrolled single center,
clinical trial to determine the safety, tolerability, and bioavailability of the RELiZORB enzyme cartridge with enteral nutrition when used daily for a total 90 days of treatment when given to pediatric subjects with SBS, aged 2 years – 18 years, who have been PN dependent for at least 6 months.

Subjects with a signed informed consent will be enrolled in the study. Results from screening must not show any clinically significant abnormalities in order for the subject to progress to the enrollment and treatment phases of the trial. During the screening visit, subjects and legal guardians will also receive education from a registered dietician on recording caloric intake and composition in oral and enteral feeds, and PN. As part of this education, the subject and parent/guardian will receive access to a nutrition/food tracking phone application (Cronometer) to assist them with this task throughout the study. If there is no electronic capability, a paper diary will be provided. The subject and parent/guardian will also receive education from a registered nurse on accurate and complete stool collection. Subjects will be provided with a standardized weight scale for at-home weight recording.

Upon completing screening and enrollment, subjects and their legal guardians will be instructed to record total calories and composition in oral and enteral feeds and TPN and to collect all stool for 72 hours (Days -3 to -1) prior to the first day of treatment. The stool collection and recording will be repeated in the 72-hours preceding the final study visit (Days 87-89). All stool will be collected in a single container and kept refrigerated during collection. If necessary (for example, out of state participants, excessively watery stools), subjects will be admitted to our dedicated research center during this collection period.

On the first day of treatment (Day 1), all subjects will use the RELiZORB enzyme cartridge to administer their enteral nutrition and will continue to use a cartridge daily for a total of 90 days. The study device will be used with enteral nutrition administered to the subject daily by a parent or guardian for 90 days (Day 1 to Day 90).

Nutritional intake (24 hour enteral and oral intake, and PN volume) will be recorded daily in the nutrition/food tracking phone application (or paper diary). Any changes in symptoms (e.g., abdominal pain, increases in stool output above baseline, changes in urine frequency/color) will also be recorded daily by the subject’s parent or guardian in an electronic diary (or paper diary). Families will also receive a daily study coordinator phone call to address any issues or concerns and ensure compliance. Subjects will visit the clinic on Day 1, Day 7, Day 14, Day 28, Day 60, and Day 90 of the treatment period, where clinical and laboratory assessments will be collected for the clinical and safety endpoints. Subjects will also receive continuing nutrition education during these visits and any questions will be addressed. The study staff (dietician, investigators) will have weekly telephone contact with families during interim weeks after the day 14 visit. Study staff will monitor safety, nutrition tracking, diaries, weekly weights, stool composition (Bristol scale) and output, changes in caloric intake, changes in urine output, and will make adjustments to PN and enteral feeding accordingly. Adjustments will be based on the subject’s nutritional needs, weight, height, hydration status and investigator’s medical judgement. If necessary, unscheduled visits can be arranged in place of the telephone contacts.

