### Secondary efficacy endpoint

The secondary efficacy endpoint is the change in body weight (weight-for-age z-score) since baseline, assessed weekly throughout the study.

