| Clinical laboratory evaluations^d^ | X |  |  |  | X |  | X |  | X |
| Dietician Education | X |  | X |  | X |  | X |  | X |
| 72-hour fecal collection^e^ |  | X |  |  |  |  |  |  | X (final visit) |
| Lipid profile^f^ | X |  |  |  | X |  | X |  | X |
| Total plasma FAs^g^ | X |  |  |  | X |  | X |  | X |
| Liver tests^h^ | X |  |  |  | X |  | X |  | X |
| Nutritional assessment | X |  | X |  | X |  | X | Weekly | X |
| Record nutritional intake^i^ |  | Daily | X | Daily | X | Daily | X | Daily | X |
| Change in PN/ enteral feeding | X | X | X |  | X |  | X | Weekly | X |
| Home Body weight (WAZ) |  |  |  |  |  |  |  | Weekly |  |
| RELiZORB |  |  | X | Daily | X | Daily | X | Daily | X |
| Adverse Events^j^ |  |  | X | Daily | X | Daily | X | Daily | X |
| Concomitant Medications |  |  | X | Daily | X | Daily | X | Daily | X |
| Assess medical/ surgical procedures | X |  | X |  |  |  | X |  | X |
| Supply Investigational Product |  |  | X |  | X |  | X |  | X |
| Review Daily Patient Diary |  |  |  |  | X |  | X | Weekly | X |

I/E criteria = Inclusion and exclusion criteria.

FAs =fatty acids.

PN = Parenteral nutrition.

^a^ Record known bowel length/type from last surgical resection or other measurement.

^b^ Blood pressure, pulse rate, respiratory rate and temperature.

^c^ Includes height or length, head circumference (for subjects < 36 months), and weight. If a physical examination or nutrition assessment was performed during the 3-day screening period, it will be used for the baseline assessment when available.

^d^ Includes chemistry (including fat-soluble Vitamins A, D, E, and K), hematology, coagulation and C-reactive protein (CRP). Clinical laboratory evaluations obtained at time of screening will serve as the baseline assessment.

^e^ 72-hour fecal collection will occur in the 72 hours preceding treatment day 1 and the final clinic visit day 90

^f^ Samples of the lipid profile will include cholesterol, high-density lipoprotein (HDL), very low-density lipoprotein (VLDL), and low-density lipoprotein (LDL). Results of samples obtained at time of screening will be analyzed during enrollment period, prior to participant receiving device.

^g^ Samples of total plasma fatty acids will include total saturated, total monosaturated, total polyunsaturated, total Omega-3, total Omega 6, total fatty acids, a-linolenic Acid, linoleic acid, oleic acid, EPA, arachidonic acid, mead acid, DHA, and triene:tetraene ratio.

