### First Day of Treatment (Day 1)

Baseline evaluations will be performed for assessment of safety and clinical endpoints.

Assessments of safety will include:

- Vital signs
  - Temperature, blood pressure, pulse rate, and respiratory rate
- Physical examination
  - Height or length, head circumference (for subjects < 36 months), and weight.
  - Physical examinations performed during the 3-day screening period will be used for baseline assessment when available

• Concomitant Medications

• Medical/ surgical procedures

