The investigator will assess the subject’s nutritional treatment, weight, growth and hydration status to determine if, based on their medical judgment, advancement of oral or enteral feeding and weaning from PN should occur. This will occur during study visits as well as through the weekly telephone contact with families. Families will be provided with a standardized weight scale at the time of inclusion of the study for consistent weight measurements.

Any AEs that occur after the start of use of the study device will be recorded according to the procedures in Section 9.0[_RECORDING_ADVERSE_EVENTS](#_RECORDING_ADVERSE_EVENTS). Any significant clinical finding prior to administration of the study device will be included in the subject’s medical history.

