### Outcomes Evaluation

Continuous outcomes, which include all outcomes except the incidence of adverse events (AEs) and incidence of weaning from PN, will be described as indicated in the general overview above using summary measures at each visit. Incidence of ever weaning from PN will be summarized by frequency count and percentage. Analysis for incidence of AEs grade 2 or higher is described in the Safety Analysis section below.

Assessment of change in continuous outcomes will be made using the area under the curve between study day 7 and 90 (AUC_7-90_), adjusted for baseline, calculated over all relevant assessment timepoints (5 and 13 post-baseline weekly assessments for measurements obtained in clinic and at home, respectively). Measurements obtained in clinic will be assessed at study days 7, 14, 28, 60 and 90, while those obtained at home will be assessed on study days 7, 14, 21, 28, 35, 42, 49, 56, 63, 70, 77, 84, 90.

Adjustment for baseline will be made by dividing the outcome value at each assessment by the baseline value, leading to interpretation of AUC_7-90_ as a mean relative percent increase or decrease in outcome depending on whether AUC_7-90_ is greater or less than unity (1), respectively. AUC_7-90_ will be calculated as a time-weighted average, given by the equation:

$$\frac{0.5\cdot\sum\left( t_{i+1}-t_{i} \right)\left( r_{i}+r_{i+1} \right)}{\sum\left( t_{i+1}-t_{i} \right)}$$

where $t_{i}$ denotes the assessment day as described above,, and $r_{i}= y_{i}/y_{1}$ denotes the outcome at assessment day $t_{i}$ divided by the baseline (day 1) value. Hypothetical examples for a single subject with reduction in outcome at each visit is shown below in Figure 3 for measurements obtained in clinic (a) and measurements obtained at home (b). The dotted lines enclose a reference AUC_7-90_=1 (indicating no change in outcome), and the gray shaded area indicates AUC_7-90_.

Figure 3. Hypothetical examples of area under the curve for one subject

| [figure not shown] | [figure not shown] |
| --- | --- |
| a. Example of in-clinic outcome assessment. | b. Example of at-home outcome assessment. |

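### Home-scale weights carry 67% to 75% of the weekly weight average but are referred to a clinic-scale baseline, and no home-scale baseline is scheduled

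*Protocol*

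**What the plan says.** - **Endpoint.** Protocol section 3.3.2: "The secondary efficacy endpoint is the change in body weight (weight-for-age z-score) since baseline, assessed weekly throughout the study".
- **Home scale.** Section 3.1: "Subjects will be provided with a standardized weight scale for at-home weight recording". Section 7.1.4 adds: "Families will be provided with a standardized weight scale at the time of inclusion of the study for consistent weight measurements".
- **Baseline weight.** Section 7.1.3 puts this in the Day 1 physical examination: "Height or length, head circumference (for subjects < 36 months), and weight". Footnote c of Table 2 allows an earlier examination to serve: "If a physical examination or nutrition assessment was performed during the 3-day screening period, it will be used for the baseline assessment when available". Both are clinic weighings.
- **Schedule of home weights.** The home body weight row of Table 2 has one entry, weekly, in the column for Days 15-27, 29-59 and 61-89. It is blank at screening, enrollment, Day 1 and every clinic visit.
- **Analysis.** Section 10.2.2 divides each value by one Day 1 value and takes a trapezoid time-weighted average over Days 7 to 90. For the clinic series: "Measurements obtained in clinic will be assessed at study days 7, 14, 28, 60 and 90". For the home series: "those obtained at home will be assessed on study days 7, 14, 21, 28, 35, 42, 49, 56, 63, 70, 77, 84, 90".
- **A second day list.** Section 10.2.4 prints the weekly days with Day 60 where section 10.2.2 has Day 56.

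The protocol does not tie the home scale to the clinic scale and sets no rule on clothing or time of day. It refers to a study procedures manual, which is not shown.

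**The concern.** The weekly series mixes two instruments and two weighing settings, while the denominator comes from only one of them. Baseline, Day 7 and Day 14 are clinic weights; after that most values are home weights. A systematic difference between home and clinic (device, clothing, time of day) therefore appears only after treatment has started, and looks like a change on treatment.

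In a randomized trial such a difference would largely cancel between arms. This trial is uncontrolled, so there is nothing for it to cancel against. A home baseline that was never taken cannot be supplied later by an analysis plan.

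**Working it through.** **1. The plan's own figures.** The plan gives no figure for this point. The counts in section 10.2.2 (5 clinic and 13 weekly assessments) agree with its two lists. The general power statement in section 10.2.5 (n = 32, mean/SD 0.51, 80% power) reproduces at 79.8% with a one-sample t-test. The plan gives no SD for the weight endpoint, so the shift below cannot be set against that detectable effect.

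**2. Which weekly values are home weights.** Weekly days (section 10.2.2): 7, 14, 21, 28, 35, 42, 49, 56, 63, 70, 77, 84, 90. Clinic days: 7, 14, 28, 60, 90. The days on both lists are 7, 14, 28 and 90. That leaves 21, 35, 42, 49, 56, 63, 70, 77 and 84, so 9 of 13 are home weights.

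**3. Their share of the average.** Under the trapezoid formula an inner day's weight is half the sum of its two gaps, and an end day's is half its one gap. The total is 90 − 7 = 83 days.

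| Reading | Home-only days | Home weight (days) | Share |
|---|---|---|---|
| Section 10.2.2 list | 9 of 13 | 8 × 7 + 6.5 = 62.5 | 62.5/83 = 75.3% |
| Section 10.2.4 list (Day 60 for 56) | 8 of 13 | 5 × 7 + 9 + 5 + 6.5 = 55.5 | 55.5/83 = 66.9% |
| Section 10.2.2 list, Day 60 ± 3 visit supplying Day 63 | 8 of 13 | 62.5 − 7 = 55.5 | 66.9% |

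In the second row, Day 49 carries 9 days and Day 63 carries 5 because of the uneven gaps around Day 60. Section 10.2.2 taken literally calls all 13 weekly values home measurements. That conflicts with Table 2 and would enlarge the mismatch.

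**4. Size of the shift (assumed inputs).** The documents give neither an offset nor a weight SD. Assume an offset of 0.1 to 0.3 kg and a weight SD for age of 1.6 kg (toddler) to 3.0 kg (child of about 20 kg). Approximately, shift in z per home reading = offset / SD, and shift in the average = share × offset / SD.

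- Low: 0.1/3.0 = 0.033 per reading; × 0.669 = 0.022.
- High: 0.3/1.6 = 0.188 per reading; × 0.753 = 0.141.

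The average moves by about 0.02 to 0.14 z with no true change. Eligibility runs to 18 years, and the shift falls in proportion as the SD rises, so doubling the SD halves it. Different assumptions (offset of 0.5% to 2% of body weight, weight CV of 11% to 16%) also give 0.02 to 0.14.

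**5. On the planned scale.** The plan analyses value divided by baseline. If the true z stays at its baseline z0, AUC = 1 + shift/z0. For a home scale that reads heavy:

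- z0 = −1: 1 − 0.022 = 0.98 to 1 − 0.141 = 0.86.
- z0 = −0.5: 1 − 0.022/0.5 = 0.96 to 1 − 0.141/0.5 = 0.72.
- z0 = +1: 1.02 to 1.14.

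Both size and direction depend on the child's baseline z.

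**The case against.** The strongest reply is that the protocol already aims at consistency. Every family gets a standardized scale, clinic weights continue at five visits, and section 10.2.2 asks for summaries at each visit. Baseline to Day 90 can therefore be read on the clinic scale alone, and a home-clinic step could be noticed. Weighing technique may be set out in the procedures manual, and the rule for combining the two series in an analysis plan. The endpoint is secondary and summarised descriptively.

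Much of this stands and limits the harm. It does not remove the mismatch. A common home scale makes homes agree with each other, not with the clinic, and a shared device could make an offset shared, which is the kind that biases a mean. Neither a manual nor an analysis plan can refer home readings to a home baseline that Table 2 does not schedule.

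Stronger readings are tempting, and the documents do not support them:

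- **That any scale difference becomes false weight change in the result.** Only a difference shared across families biases the cohort mean. Differences that vary by family mainly add variance.
- **That a heavy-reading home scale must appear as a gain.** With a negative baseline z it lowers the planned ratio.
- **That the bias is known to be 0.14 z or thereabouts.** No document reports an offset.
- **That nine of 13 and 75% are settled.** They follow from Table 2 with one of two printed day lists.
- **That the primary endpoint is biased.** Home weights do inform nutritional adjustments, so an indirect route exists, but nothing in the documents shows its size.

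**Conclusion.** The point holds as a gap in data collection. On the Table 2 schedule, 8 or 9 of the 13 weekly weights, with 67% to 75% of the averaging weight, are home readings referred to a single clinic baseline. Any offset common to families would enter the secondary estimate in that proportion, with no control arm to remove it.

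The potential size, 0.02 to 0.14 z, rests wholly on the assumed offset and SD, covers younger children, and is not itself on the planned ratio scale. The passages that define home and clinic days also disagree and need reconciling. This is a worthwhile, inexpensive improvement to a secondary endpoint. It does not show that the endpoint is wrong.

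**What to change.** 1. **Collect a home baseline.** Schedule home-scale weights before first device use, on Days -3 to -1, preferably repeated. Subjects admitted to the research center for the stool collection cannot weigh at home then; for them, use the issued scale on Day 1. Alternatively, pair home and clinic weights at more than one visit.
2. **Refer each series to its own baseline**, home to home and clinic to clinic. With no true change, a constant offset then leaves the ratio at 1. Moving the single baseline to the home scale would not be enough. On the section 10.2.2 list the four clinic values, 20.5/83 = 24.7% of the weight, would then carry the offset with the opposite sign.
3. **Amend the text to match.** Add the weighing to Table 2, change the definition of y1 in section 10.2.2, and state which weekly days are home and which are clinic. Use one day list in sections 10.2.2 and 10.2.4.

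The cost is a few extra readings per family, a small change to the analysis, and no new equipment, since the scale is issued at inclusion. A correction based on one paired reading passes that reading's error to all of the child's home values, which is why repeated readings are preferable.
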